### Outcome Measure

#### Alcohol Use and Experience

Alcohol use and experience will be evaluated using the 17 items in the Alcohol Attitudes and Behavior survey before and after the intervention. These items are adapted from the Centers for Disease Control and Prevention’s Behavioral Risk Factor Surveillance System Questionnaire and Global School-based Student Health Survey [23,24]. Alcohol use will be measured by an item on the 30-day recall dosage of alcohol consumption. Reasons for drinking, experience in drinking, and other relevant information will be surveyed with the rest of the 16 items. These items have been used in a national study in China [23,24].

#### Attitude Toward Alcohol Use

Attitude towards alcohol use will also be measured with the Alcohol Attitudes and Behavior survey, which includes 15 items adapted from the Scale for the Measurement of Attitudes Toward Alcohol designed to assess that attitude in three domains: sociability, personal unease, and economic aspects [25]. The scale has been validated among adolescents and has demonstrated good internal consistency (Cronbach alphas ranging from .79 to .91) and valid factor structures. Both domain-specific scores and the total score will be used in analysis. We have already gone through a standard procedure for piloting the questionnaire. To ensure the validity of the survey among Chinese adolescents, we have gone through a standard piloting procedure [26]. Briefly, we have invited professional Chinese translators with experience in public health to translate the questionnaire into traditional Chinese, which was then examined and back-translated into English by the research team. The back-translated version of the questionnaire was checked by the research team again to ensure the language accuracy. The Chinese version of the questionnaire was reviewed by a local expert panel using the Delphi process. The expert team included pediatricians, public health experts, parents of adolescents, and secondary school teachers. After reaching consensus with the expert team, the questionnaire was piloted to adolescents to fine-tune the wording and presentation.

#### Number of Successful Referrals per Participants

When making a referral, a participant will need to provide their unique referral code. The new participant who receives this code will then input it during registration. Our website server will record all of these unique referral codes, which will allow us to subsequently analyze the referral pathways and calculate the number of successful referrals per participant.

Since the change in attitudes and behaviors could vary with age, the above analysis will also be carried out for each grade separately.

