## Methods

### Study Design

The proposed study will consist of a cluster randomized controlled trial on the effectiveness of an Internet quiz competition in promoting healthy attitudes and behaviors towards alcohol use among adolescents. As the intervention website could be referred by participants, cluster randomization, instead of individual-level randomization, is chosen to minimize treatment contamination. The study will employ an Internet viral marketing strategy to maximize sample size. In total, 24 schools (6552 Grade 7-9 students) will be recruited with the collaboration of our community partners such as the Tung Wah Group of Hospitals. Considering that the average number of students in one secondary school class is 35 and that there are four classes in each grade, a total of 10,080 students (24×3×4×35) will be reached. Assuming a response rate of 65%, the number of effective campaign starters will be 6552. Students who cannot comprehend basic Chinese and Cantonese will be excluded.

Half the schools will be randomized for the Internet quiz competition campaign (intervention arm) and half will be randomized for an information package (control arm). Students in the intervention group will be given the opportunity to take part in the online quiz competition and refer others to join the campaign, whereas those in the control group will receive an electronic information package containing comparable information as the intervention arm. All participating students’ demographics and change in attitude and behavior will be measured by questionnaire surveys before intervention, within 1 month, and between 2-3 months after intervention. A longer-term follow-up (12 months after intervention) will also be attempted if schools are willing to commit and resources allow. Weblog data will also be collected from website servers for subsequent analysis of the effectiveness of the Internet viral marketing strategy. Figure 1 is a flowchart of the proposed study.

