### Power Analysis

Considering an attitude difference in 50% of the pooled standard deviation (SD) to be minimally satisfactory, we will need a sample size of 128 to examine, via a two-sample independent *t* test, whether the campaign is more effective than a traditional promotion strategy at a .05 significance level and 80% power [19]. Due to our cluster study design, intraclass correlation (ICC) needs to be addressed. It was reported that an ICC of attitude-related construct among schools was about 0.092 [20], which inflates the required sample size to N=n×[1+(K‒1)×ICC]=128×[1+(3×4×35‒1)×0.092]≈5063. Hence, the number of starters to be recruited (6552) will be sufficient to achieve the study’s primary aim regardless of the number of referrals.

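### Possible variation of the effect with age is addressed only by repeating the analysis within each grade, which does not test whether the effect differs between grades.

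*Protocol article*

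**What the plan says.** The last paragraph of Number of Successful Referrals per Participants (protocol article, Outcome Measure) reads: "Since the change in attitudes and behaviors could vary with age, the above analysis will also be carried out for each grade separately". It names no test of whether effects differ between grades, and none appears elsewhere in the article.

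The reference to the analysis above is loose. The sentence sits under the referral outcome, and the only comparison method the article describes is the two-sample t test under Power Analysis. Since the sentence itself speaks of attitudes and behaviors, I read it as the comparison of arms on those outcomes, repeated in Grades 7, 8 and 9.

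Power Analysis covers the overall comparison only: "Considering an attitude difference in 50% of the pooled standard deviation (SD) to be minimally satisfactory", tested "at a .05 significance level and 80% power", with an allowance for clustering because "an ICC of attitude-related construct among schools was about 0.092".

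**The concern.** The method does not match the reason given for it. Whether an effect varies with age is a question about differences between grades. Three separate comparisons give three answers to another question: is there an effect in this grade? A significant result in one grade and a non-significant one in the next is not evidence that the two effects differ. Equally, three significant results do not show that the effects are the same.

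At stake is a possible report that the campaign works in some grades only, when its effect is the same in all. The article's Conclusion looks ahead to use in the mainstream secondary school curriculum, so such a report could influence which grades are offered the programme. The separate analyses also leave a feature of the design unused: each school contributes all three grades, so effects can be compared between grades within schools.

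**Working it through.** **Inputs from the article.**
- Schools: "24 schools (6552 Grade 7-9 students) will be recruited", with half to each arm, so 12 per arm (Study Design).
- Students: "the average number of students in one secondary school class is 35 and that there are four classes in each grade", so 4 × 35 = 140 per grade and 3 × 140 = 420 per school.
- Response 65% (Study Design): 0.65 × 140 = 91 per grade per school.
- ICC 0.092 and effect 0.5 SD (Power Analysis).

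**Assumptions.** The ICC of 0.092 is applied to students of the same school and grade. The share of school variance common to the three grades is not in the article, so it runs from 0 to 1. Tests are two-sided; the article does not say so, but its sample size fits this.

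**The plan's own figure.** A two-sided t test for 0.5 SD at 80% power needs 64 per arm, matching "we will need a sample size of 128". The design effect is 1 + (420 − 1) × 0.092 = 39.548, and 128 × 39.548 = 5062.1, against the stated 5063. Both figures reproduce.

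**Power within one grade.** Effective number per arm = 12 × 91 / (1 + 90 × 0.092) = 1092 / 9.28 = 117.7. With 22 degrees of freedom, power at 0.5 SD is 0.956, against 0.966 for all grades together. The ICC dominates, so splitting by grade costs little power.

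**How often would grades disagree when the effect is identical?** School-by-grade means were simulated (40,000 trials per setting), with a t test on 22 degrees of freedom in each grade. Mixed means that one or two of the three grades are significant.

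| True effect in every grade (SD) | Power per grade | Mixed, none shared | Mixed, half shared | Mixed, 80% shared | Mixed, fully shared |
|---|---|---|---|---|---|
| 0 | 5% | 14.2% | 12.6% | 10.1% | 6.5% |
| 0.1 | 11% | 30.5% | 24.0% | 18.0% | 10.6% |
| 0.2 | 31% | 63.9% | 46.9% | 32.9% | 19.4% |
| 0.25 | 45% | 74.3% | 53.6% | 37.5% | 21.9% |
| 0.3 | 59% | 72.0% | 52.4% | 36.6% | 21.5% |
| 0.4 | 83% | 41.5% | 31.8% | 23.1% | 13.7% |
| 0.5 | 96% | 12.9% | 11.0% | 8.2% | 5.3% |

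With no effect at all, at least one grade is significant in 9% (fully shared) to 14% (none shared) of trials.

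**The same trials with an interaction test.** A test of the within-school grade contrasts between arms (Hotelling T²) declared a difference in 4.7% to 5.3% of trials in every setting.

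**Precision of a grade difference.**
- One grade's effect: SE = √[2 × (0.092 + 0.908/91) / 12] = 0.130 SD.
- Two such estimates treated as independent: √2 × 0.130 = 0.184 SD.
- Within schools: SE = √[4 × (v + 0.908/91) / 12], where v is the school variance not shared by grades. Fully shared (v = 0) gives 0.058 SD; half shared (v = 0.046) gives 0.137 SD; none shared (v = 0.092) gives 0.184 SD.

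**Sensitivity.** The Abstract gives 20 schools, not 24. With 20 schools and the same 91 per grade, power per grade is 0.91 at 0.5 SD and 0.51 at 0.3 SD.

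**The case against.** The best defence has four parts.

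1. **The grade analyses are additional.** The sentence says the analysis will also be run by grade. It does not say that grades will be compared by their significance, or that an age difference will be declared. Age variation is not among the stated aims. This stands: it limits what can be attributed to the authors, and it makes the matter secondary.

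2. **At the trial's own effect size the risk is small.** At 0.5 SD each grade has about 96% power, and mixed results arise in 5-13% of trials. With school variance fully shared, that is no worse than the interaction test. This stands. However, the article presents 0.5 SD as the smallest satisfactory difference, not as a forecast. The control arm receives comparable information, so a smaller effect is possible.

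3. **The gain in precision is not assured.** If the grades share no school variance, the within-school SE equals the independent one, 0.184 SD. This also stands. The reason for the change is that the interaction test answers the question; any gain in precision is extra.

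4. **An interaction test may be in the full protocol or analysis plan, which are not shown.** Its absence from the article is therefore no error in itself. But the article is not silent here: it gives a reason and fixes a method, and that method does not serve the reason.

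**Conclusion.** The point holds in a limited form. Separate analyses by grade do not test whether the effect differs between grades, and the article names no other method although possible variation with age is its reason for them.

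The consequence depends on the true effect. With an identical effect in all grades, a mixed pattern of significance would appear in about 5-13% of trials at 0.5 SD, 14-42% at 0.4 SD and 22-74% at 0.25-0.3 SD, against about 5% with an interaction test. Each range covers the unknown share of school variance common to the grades. Effects below 0.5 SD are my assumption. The figures apply to the attitude score only, because the article gives no SD or ICC for drinking.

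A reader might infer that the trial will often report grade differences that do not exist. The documents do not support that: at the planning value such patterns are uncommon, and nothing says that grades will be judged by comparing their significance. The primary comparison is unaffected.

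**What to change.** Fit one mixed model on all students, with arm, grade and arm-by-grade terms and random effects for school and for school-by-grade. Take the degrees of freedom for the interaction from the number of schools, not of students. Base any statement that the effect varies with age on the arm-by-grade test. Show the grade-specific estimates from that model with confidence intervals, labelled as supportive.

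The sentence should also name the outcomes it covers, since it now stands under the referral count.

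This changes analysis wording only; grade and school are already part of the design, and no new data are needed. The cost is that a significant result in a single grade can no longer be claimed on its own.

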### Covariates

Owing to randomization, the confounding effect should be minimized. However, we will still evaluate school-level covariates for data analysis. The covariates we will collect include the number of health education lessons related to alcohol, the school neighborhood socioeconomic factors as extracted from 2011 Hong Kong Population Census, and the school academic quality as operationalized by the university admission rate for each school.

## Results

The project was funded by the Health and Medical Research Fund of the Food and Health Bureau, Hong Kong government, in July 2015. Enrollment started September 2015, and results are expected by July 2017.

## Discussion

### Principal Considerations

Alcohol consumption is prevalent among adolescents in Hong Kong. The prevalence of underage drinking is rising globally, according to the World Health Organization. The rise of underage drinking in Hong Kong has been particularly alarming since the alcohol duty reduction in 2008. It is therefore of the utmost importance that children and adolescents be informed of the harmful effects of excessive alcohol use, particularly at a young age.

The aim of the proposed study is to find a cost-effective way of tackling the problem. With the Internet increasingly being recognized as a practical and cost-effective platform for health information delivery, we expect our Internet-based intervention to significantly alter adolescents’ attitudes towards alcohol. It is important to provide accurate alcohol-related knowledge early in adolescence. Research shows the correlation between attitudinal and behavioral changes. Promoting better attitudes toward alcohol use among adolescents may lead to changes in drinking behavior, thereby mitigating the local underage drinking problem.

### Conclusion

The local resources available for school-based alcohol education are relatively minimal. The proposed study will offer an innovative, cost-effective method of raising adolescents’ awareness of the harmful effects of excessive alcohol assumption. The project will be carried out in collaboration with an academic institution and a non-government organization and will involve shared resources, the exchange of best practices, and joint efforts towards sustainability. In the long term, the aim is for the online alcohol education platform to be funded on an ongoing basis and to be incorporated into Hong Kong’s mainstream secondary school health education curriculum. The platform can also be adapted to deliver health-related information in other learning areas such as physical activities, drug use, and safe sex in the near future.

## Abbreviations

ELM: Elaboration Likelihood Model
ICC: intraclass correlation
